### Sample size

The sample size has been calculated using G*Power version 3.1.0, with an alpha level of 0.05 (one-tailed) and a study power of 80%. As no previous studies have addressed the effects of CBT in reducing FoF in stroke populations, the effect size used to calculate the sample size is the same as that calculated for our pilot sample of ten subjects (0.26), in which five subjects received the CBT, another five subjects received the GHE, and both groups received 45 min of TOBT. The ABC-C [34] is the primary outcome measure at eight weeks after the end of treatment. The required sample will, thus, comprise 76 subjects, with 38 per group. With reference to previous clinical trials [30, 40], we expect the dropout rate to be about 15%, requiring an extra six subjects per group to be recruited. Therefore, the planned sample size is 88.

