**Methods:**

The study will constitute a placebo-controlled single-blind parallel-group randomized controlled trial in which patients are assessed immediately, at 3 months, and at 12 months. The selected participants will be randomly allocated into one of two parallel groups (the experimental group and the control group) with a 1:1 ratio. Both groups will receive 45 min of TOBT twice per week for 8 weeks. In addition, the experimental group will receive a 45-min CBT-based group intervention, and the control group will receive 45 min of general health education (GHE) twice per week for 8 weeks. The primary outcome measure is subjective balance confidence. The secondary outcome measures are fear-avoidance behavior, balance ability, fall risk, level of activities of daily living, community reintegration, and health-related quality of life.

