### Data analysis

The data will be double-entered to enable validation. Simple descriptive statistics will be used to summarize the sociodemographic characteristics of the participants and other variables of interest. The normality of the data will be examined by a Kolmogorov–Smirnov test. Between-group comparisons at baseline will be performed using *t* tests, Kruskal–Wallis tests, chi-square tests, or Fisher’s exact test, as appropriate.

To measure the changes over time in variables of interest between the two study arms, mixed-effects models with adjustments for potential confounding variables, such as sociodemographic characteristics, will be used. Mixed-effects models go beyond the customary linear framework by incorporating random effects relating to participants. They account well for intra-correlated repeated measures data and accommodate missing data caused by dropouts, as long as the data are missing at random. Pearson and Spearman’s correlation tests, as appropriate, will be used to investigate the correlations between outcome variables. SPSS 17.0 will be used for the remaining statistical analysis, with a 5% level of confidence (two-sided) accepted for significance.

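### The sample size of 76 at 80% power does not follow from the stated inputs, and 80% is not supported for a two-sided comparison at one visit

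*Protocol article*

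**What the plan says.** All statements are in the protocol article.

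- **Sample size, software and error rates:** "The sample size has been calculated using G*Power version 3.1.0", "with an alpha level of 0.05 (one-tailed) and a study power of 80" per cent.
- **Sample size, effect:** "the effect size used to calculate the sample size is the same as that calculated for our pilot sample of ten subjects (0.26". In that pilot "five subjects received the CBT, another five subjects received the GHE". The metric is not given.
- **Sample size, endpoint:** "The ABC-C [34] is the primary outcome measure at eight weeks after the end of treatment".
- **Sample size, result:** "The required sample will, thus, comprise 76 subjects, with 38 per group". This is raised to 88 for dropout.
- **Data analysis:** mixed-effects models on the repeated measures, adjusted for possible confounders, "with a 5% level of confidence (two-sided) accepted for significance".
- **Measurements:** five occasions, namely baseline, mid-treatment, end of treatment, 12 weeks after and 12 months after. The abstract names three post-treatment assessments, which makes four with baseline.
- **Abstract, Methods:** two arms, "the experimental group and the control group) with a 1:1 ratio".

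**The concern.** The section presents 76 as the consequence of the inputs just listed. Read as written, those inputs describe two equal groups compared once on ABC-C with a one-tailed test, and that comparison does not give 76 at 80% power. The planned test is also two-sided, which lowers power further.

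The 80% figure governs how a null result will be read. If the real chance of detecting the planned effect is lower, a non-significant difference says less against CBT than readers will assume.

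**Working it through.** **Inputs from the article.** Effect size 0.26; one-tailed alpha 0.05; power 80%; 38 per arm; two-sided 5% in the analysis; five measurements. **Assumed, because not stated:** the metric of 0.26, the test and any correlation.

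**Step 1. Try to reproduce 76 from the inputs as written.** For a two-sample t test with n per arm, the noncentrality is d × √(n/2) on 2n − 2 degrees of freedom. At n = 38, √(38/2) = 4.359, and the critical value is 1.666 one-tailed or 1.993 two-sided.

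| Reading of 0.26 | d | Noncentrality at 38 per arm | Power, one-tailed | Power, two-sided | Total for 80%, one-tailed | Total for 80%, two-sided |
|---|---|---|---|---|---|---|
| Cohen's d | 0.26 | 1.133 | 30% | 20% | 368 (184 per arm) | 468 |
| Cohen's f (d = 2f) | 0.52 | 2.267 | 73% | 61% | 94 (47 per arm) | 120 |

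Reading 0.26 as r, f-squared or eta-squared gives one-tailed totals of 88, 26 and 20. A correlation test needs 91 and a paired t test 93. None gives 76.

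**Step 2. Look for added assumptions that return 76.**

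*Repeated-measures ANOVA, between factors, 0.26 as f.* λ = f² × N × m / (1 + (m − 1)ρ). With N = 76, m = 4 and ρ = 0.5, λ = 0.0676 × 76 × 4 / 2.5 = 8.22, and the F test on 1 and 74 degrees of freedom has 80.8% power. At N = 74 it has 79.7%, so 76 is the answer with equal arms. With ρ = 0.5, m = 3 gives 80 and m = 5 gives 72. With m = 4 and ρ = 0.7 the total is 92, and 76 gives 71.9% power.

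*One-tailed baseline-adjusted comparison, 0.26 as f.* With baseline correlation r, the effective d is 0.52 / √(1 − r²). At r = 0.44 this is 0.52 / 0.898 = 0.579. Noncentrality is 0.579 × 4.359 = 2.52 and one-tailed power is 80.4%. The total is 76 for r from 0.43 to 0.45 (80 at 0.40, 70 at 0.50). Two-sided power in that range is about 70%.

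*Other combinations.* The same F test at alpha 0.10, the counterpart of one-tailed 0.05, returns 76 with m = 2, ρ = 0.6 and with m = 3, ρ = 0.7. At alpha 0.05 each then has 70.6% power. With 0.26 as d, the one-tailed adjusted total is 134 at r = 0.8 and 72 at r = 0.9, so 76 would need r just below 0.9.

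The recurring 70% is no accident. In the normal approximation, a one-tailed 5% test with 80% power has noncentrality 1.645 + 0.842 = 2.487. Against the two-sided limit, 2.487 − 1.960 = 0.527, which is power of about 70%.

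**Step 3. Power of 38 per arm for one visit, two-sided 5%, by assumed baseline correlation.**

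| r | 0.26 as f | 0.26 as d |
|---|---|---|
| 0 | 61% | 20% |
| 0.5 | 73% | 25% |
| 0.6 | 80% | 29% |
| 0.7 | 88% | 35% |

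Without adjustment, the smallest d with 80% power is 0.65 two-sided (0.58 one-tailed).

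**The case against.** The strongest reply is that 76 is obtainable, so no arithmetic error is proven. A standard repeated-measures routine returns exactly 76 with f = 0.26, and its four measurements fit the abstract and the longitudinal analysis. A baseline-adjusted test also returns 76 while keeping one tail and one time point. The article names no test and plans adjusted models. It is also a condensed report, and the metric, routine and correlation may stand in a full protocol or analysis plan that is not shown.

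Much of this stands. A reader might infer that the trial's power is simply wrong, or that it is really 20% or 61%. The documents do not support that. The 20% figure needs 0.26 to be d, which the article never says, and the 61% figure assumes no gain from baseline. If 0.26 is f and the baseline correlation is about 0.6 or higher, 80% is reached even two-sided.

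It does not dispose of the point. The exact repeated-measures match conflicts with the article's own text: that F test is not one-tailed, it compares averages over visits rather than one time point, and it uses four measurements where the Measurements section lists five. The one-tailed routes fit the Sample size section better, but leave about 70% power under the two-sided test in the Data analysis section. The point therefore rests on stated inputs, result and analysis that do not agree, and not on missing detail alone.

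**Conclusion.** The point holds in this form. In an unadjusted comparison at one time point, the stated inputs do not give 76 (368 as d, 94 as f). Every route to 76 that I found adds assumptions the article does not state. My search was not exhaustive, so the authors' actual calculation remains unknown.

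The stated 80% is therefore unsupported for a two-sided comparison of ABC-C at a single visit, which is not the same as shown to be false. Its plausible size is 61% to 88% if 0.26 is f and 20% to 35% if it is d. These ranges assume 76 evaluable subjects, equal arms and a baseline correlation between 0 and 0.7. That correlation range is mine, since the article gives none.

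**What to change.** Rewrite the Sample size paragraph as follows:

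1. State whether 0.26 is d or f, and name the test, the number of measurements and the assumed correlation.
2. Name the primary contrast as ABC-C at one scheduled visit, tested two-sided at 5%. The time point now given, eight weeks after treatment ends, is not among the five occasions in the Measurements section and should be reconciled with them.
3. Restate the power of 76 evaluable subjects for that contrast over a range of baseline correlations, as in Step 3, with the unadjusted minimum detectable d of about 0.65.
4. Claim 80% only if the disclosed assumptions support it for that contrast.

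The cost is a rewritten paragraph and possibly a less favourable stated power. Recruitment need not change.

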### Null hypothesis

The null hypothesis will be that the efficacy of CBT combined with TOBT does not differ significantly from that of GHE combined with TOBT in promoting balance self-efficacy, thus reducing fear-avoidance behavior, enhancing balance ability, reducing fall risk, and improving community reintegration and health-related quality of life for people with stroke.

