### Measurements

All of the participants will be required to undergo five sets of measurements (Fig. 1): (i) before assessment (baseline treatment), (ii) after eight sessions of treatment (midway through treatment), (iii) after 16 sessions of treatment (end of treatment), (iv) 12 weeks after treatment (follow-up), and (v) 12 months after treatment (follow-up). All of the assessment procedures will be performed by a research assistant blind to the group allocation and not previously involved in the delivery of the interventions.

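### The only stated primary time point, eight weeks after the end of treatment, matches no scheduled assessment, so the primary endpoint cannot be measured as written

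*Protocol article*

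**What the plan says.** The Sample size section of the protocol article states that the ABC-C "is the primary outcome measure at eight weeks after the end of treatment".

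The Measurements section gives the full calendar. It announces that "All of the participants will be required to undergo five sets of measurements" and lists them. The first is at baseline and the second is "ii) after eight sessions of treatment (midway through treatment". The remaining three are "iii) after 16 sessions of treatment (end of treatment), (iv) 12 weeks after treatment (follow-up), and (v) 12 months after treatment (follow-up".

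The Abstract gives a shorter version of the same schedule: "patients are assessed immediately, at 3 months, and at 12 months".

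The section on randomization and blinding, which also describes the training, puts the 16 sessions within 8 weeks. The Primary outcome measure section names the ABC-C without a visit. The Data analysis section plans mixed-effects models for change over time between the arms and names no primary visit.

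**The concern.** A primary endpoint is a variable together with a time. The variable is clear. The time is stated once, and it falls where nobody will be measured. Whoever carries out the analysis has to substitute another visit, and the article gives no rule for the substitution.

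The two nearest candidates ask different questions. The end-of-treatment visit measures the immediate effect of adding CBT. The visit 12 weeks later measures whether the effect lasts. The Background reports that earlier stroke studies with follow-up found no retention effect, so the choice could decide the trial's conclusion. If the choice stayed open until results were known, the nominal 5% error rate would no longer hold. The power statement is also attached to a measurement that will not be taken.

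**Working it through.** **1. The calendar.** Inputs: two sessions per week, 16 sessions, 8 weeks of treatment (Abstract; Randomization and blinding); the visit list (Measurements); the stated primary time (Sample size). Weeks are counted from the start of treatment.

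| Event | Week |
|---|---|
| (i) Baseline | 0 |
| (ii) After 8 sessions | 8 / 2 = 4 |
| (iii) After 16 sessions, end of treatment | 16 / 2 = 8 |
| **Stated primary time point** | **8 + 8 = 16** |
| (iv) 12 weeks after treatment | 8 + 12 = 20 |
| (v) 12 months after treatment | about 8 + 52 = 60 |

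No visit falls at week 16. Visit (iii) is 8 weeks too early and visit (iv) is 4 weeks too late. The Abstract's immediate, 3-month and 12-month assessments agree with this table and add nothing at week 16. The schedule figure is not available in the text, but the Measurements section spells the schedule out in words.

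**2. What an open choice between the two nearest visits would cost.** Suppose success could be claimed at visit (iii) or visit (iv), each tested two-sided at 5%. Under the null hypothesis the two test statistics are approximately standard normal with correlation ρ, and

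false-positive rate = 1 − P(|Z₁| ≤ 1.96 and |Z₂| ≤ 1.96).

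- Independent: 1 − 0.95² = 0.0975, or 9.8%.
- ρ = 0.5: 9.1%.
- ρ = 0.8: 7.8%.

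The article gives no between-visit correlation. The range 0.5 to 0.8 is an assumption.

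**3. Whether the stated sample size belongs to a single visit.** The plan's figure is 76 (38 per group), from an effect size of 0.26, one-tailed alpha 0.05 and 80% power. The metric of the 0.26 is not stated.

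- For two means at one visit, n per group = 2(1.645 + 0.842)² / d². With d = 0.26 this is 183. If 0.26 is Cohen's f, then d = 2 × 0.26 = 0.52 and n = 46. Neither gives 38.
- The figure 76 does appear for a repeated-measures between-groups test with f = 0.26, alpha 0.05, 4 measurements and correlation 0.5. The noncentrality is 0.26² × 76 × 4 / (1 + 3 × 0.5) = 8.22, with power 80.8%; at N = 74 power is 79.7%. The article states neither the 4 measurements nor the 0.5. Other unstated combinations also reach 76, for example 3 measurements with correlation 0.7 when the F test is run at 0.10. All of these test an average over visits.
- With 38 per group at one visit and no covariates, one-sided power is 30% (d = 0.26) or 73% (d = 0.52). At the two-sided 5% level given under Data analysis it is 20% or 61%.
- Adjustment for baseline ABC-C would help. For a baseline correlation r, the one-sided requirement for d = 0.52 becomes 46(1 − r²), which is 34.5 at r = 0.5. For d = 0.26 it is 183(1 − r²) = 137 at r = 0.5, still far above 38. The value r = 0.5 is again an assumption.

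The calendar contradiction does not depend on step 3. That step shows only that naming a single visit does not automatically inherit the stated 80% power.

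**The case against.** The strongest reply is that this is a slip of wording. Eight weeks is exactly the length of treatment, so the sentence probably meant week 8, the end of treatment. That is the likeliest reading. It is not settled, however: the sentence places the time after treatment has ended, and the 12-week follow-up is closer to the stated date (4 weeks away against 8).

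A second reply is that a condensed article may leave the primary visit and the model contrast to a full protocol or SAP. This would answer a complaint that detail is missing, and for that reason the unnamed contrast under Data analysis is not counted here as a fault. It does not answer a time point that is stated and conflicts with the article's own schedule.

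Three stronger readings are tempting, and the article does not support them.

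- *That no primary endpoint is defined at all, because the Null hypothesis section joins several domains* ("in promoting balance self-efficacy, thus reducing fear-avoidance behavior, enhancing balance ability, reducing fall risk, and improving community reintegration"). The Abstract and the outcome sections make balance confidence the sole primary outcome and list the other domains as secondary. Only the time is in doubt.
- *That significance at any of four post-baseline visits would count.* That would give about 11% to 16% for correlations of 0.8 to 0.5. Nothing in the article says so, and the four include the mid-treatment visit, which cannot stand for a time after treatment.
- *That the visit will be picked after seeing the data.* It may have been fixed in a document not shown. The article also assigns the analysis to someone blind to allocation, which reduces the risk of selective choice without removing it.

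**Conclusion.** The statement is wrong as written. The only sentence that gives the primary outcome a time puts it at about week 16, where no assessment is planned, and the article leaves two candidate visits with different meanings. This rests on the text alone and needs no assumption.

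The size of the statistical risk is conditional. If either of the two nearest visits could be used at 5%, the false-positive rate would be about 8% to 9%, given assumed correlations of 0.8 to 0.5 and approximately normal test statistics. This bounds what the open choice could cost. It is not a prediction of what the investigators will do.

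The practical weight is moderate: a wording slip is the probable cause and the correction is cheap. It still has to be made, because the time point determines what the primary result means.

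**What to change.** Before unblinded analysis, replace the sentence under Sample size with one that names a scheduled visit. If the sponsor confirms the likely intent, it could read: *The primary endpoint is the ABC-C score at the end-of-treatment assessment (visit iii, after 16 sessions, week 8).* If the 12-week follow-up was meant, name visit (iv) instead.

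Then make the Measurements, Primary outcome measure, Data analysis and Sample size sections agree. State that the primary comparison is the between-arm difference in ABC-C at the named visit, estimated from the planned mixed model, and that ABC-C at the other visits is secondary.

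The edit takes a few sentences and by itself adds no visit and no participant. Its one real cost is that the sample-size statement must be checked for the single-visit comparison and, if needed, restated with the metric of the 0.26, any repeated-measures or baseline correlation used, and the resulting power.

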## Discussion

FoF and actual falls create a vicious cycle with devastating consequences for patients with chronic stroke. In the community under study, more than half of the patients with stroke experience impaired subjective balance confidence and have suffered at least one fall since discharge. Interventions for fall prevention have focused on balance training, leaving the FoF of stroke survivors under-addressed. The aim of the proposed clinical trial is to evaluate the effectiveness of a combination of TOBT and CBT in reducing FoF, and in turn reducing fear-avoidance behavior, increasing balance, enhancing engagement in ADL, decreasing fall risk, promoting community reintegration, and enhancing the quality of life of patients with chronic stroke.

CBT is a form of clinically proven psychotherapeutic intervention designed to shape patients’ thinking and actions to achieve therapeutic goals. Research has shown that multidimensional programs with CBT components provide an effective means of treating FoF and reducing the incidence of falling among healthy older adults. This sheds light on the effects on stroke recovery of CBT combined with customary physical training. The inclusion of CBT with customary physical training will help to break the vicious cycle of FoF and actual falls and thus, enhance the rehabilitative outcomes of patients with chronic stroke.

One of the limitations of this study is not collecting data on actual falls. However, the main purpose of this study is to evaluate the augmenting effects of CBT on existing physiotherapy in enhancing subjective balance confidence. The occurrence of post-stroke falls is a complex issue involving the interplay between physical, psychological, behavioral, and environmental factors. Future studies could further examine the roles of subjective balance confidence in developing fall prevention strategies for patients with stroke. Besides, this study may involve community-dwelling stroke patients with a range of balance ability levels. Thus, the use of BBS may not be adequately sensitive to capture the balance improvement among subjects with mildly affected balance ability.

It is hoped that the results of this study will provide scientific evidence supporting the use of CBT to augment the effects of physiotherapy in enhancing subjective balance confidence and thus, stroke rehabilitation. If effective, our intervention will offer a safe, cost-effective, and readily transferrable therapeutic approach to clinical practice that reduces fear-avoidance behaviors and fall risk, improves balance and level of independence, enhances health-related quality of life, and decreases associated healthcare costs.

### Trial status

Recruitment started in October 2016. We target to complete recruitment during 2017.

## Abbreviations

ABC-C: Chinese version of the Activities-specific Balance Confidence Scale
ADL: Activities of daily living
BBS: Berg Balance Scale
CBT: Cognitive behavioral therapy
CIM-C: Chinese version of the Community Integration Measure
FoF: Fear of falling
GHE: General health education
IADL-C: Lawton Instrumental Activities of Daily Living (Chinese version)
RCT: Randomized controlled trial
SAFFE-C: Chinese version of the Survey of Activities and Fear of Falling in the Elderly
SF36-C MCS: Mental component of the Chinese version of the Short Form General Health Questionnaire
SF36-C PCS: Physical component of the Chinese version of the Short Form General Health Questionnaire
S-PPA: Short-form Physiological Profile Assessment
TOBT: Task-oriented balance training
